**IV antibiotics efficacy sensitivity analysis**

- The primary efficacy analysis described above will be repeated with received IV antibiotics in last 24h/not fitted as a fixed effect (factor)

**Deviation from randomised strategy sensitivity censoring analysis**

- The primary efficacy analysis described above will be repeated with individuals censored at the point of deviation from randomised strategy if deviation rates are above 15%.

**Deviation from randomised strategy multiple imputation analysis**

- The primary efficacy analysis described above will be repeated using multiple imputation on individuals censored at the point of deviation from randomised strategy if deviation rates are above 15%.

**Deviation from randomised strategy multiple IPW analysis**

- The primary efficacy analysis described above will be repeated using IPW analysis on individuals censored at the point of deviation from randomised strategy if deviation rates are above 15%.

**Bayesian analysis**

- Primary outcome main analysis will also be conducted in a Bayesian framework using ACCEPT analyses (5) reporting the probability that one treatment arm is more effective than another treatment arm based on a continuous range of efficacy thresholds.
- Models will be fitted as the primary analyses above.
- Sensitivity analysis to prior assumptions will be performed using non-informative, optimistic and sceptical priors (see appendix for details). The analysis will focus on non-informative

priors, with informative priors used for sensitivity analysis, unless there are model fitting issues with non-informative priors.

- Posterior probability curves will be created for each factor compared to SOC and between arms within a factor.
- The posterior probability of each arm truly being better than the comparator will be calculated for each factor arm compared to SOC and between arms within a factor.

### **Subgroup analyses**

Subgroup analyses will be:

#### **Maternal**

- HIV
- Antibiotics since admission
- Rupture of membranes at enrolment
- Prolonged rupture of membranes (>18h)
- Offensive liquor

#### **Neonatal**

- Maternal HIV status
- Mother received antibiotics in labour
- Prolonged rupture of membranes (>18h)
- Offensive liquor
- Age at enrolment
- Estimated gestational age at labour
- Where admitted
- Any antibiotics prescribed before enrolment since birth
- Chlorhexidine cord care given

The main effect will be fitted as above for the primary analysis with additional main effect of subgroup. The interaction between subgroup and each factor (antiseptic and frequency) will also be fitted one at a time, in separate models. Interpretation of results will take multiple testing and statistical power into consideration.

### **4.7. Secondary efficacy outcome analyses**

Note that no efficacy outcome data will be presented at the interim analysis.

Analysis of bacterial load in neonates exposed to maternal antiseptic will be as per primary outcome analyses described above.

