#### Secondary outcome measures:

Mothers:

- Maternal toxicity – score and grade (Tolerability and safety)
- Change in neonatal skin bacterial load in neonates exposed to maternal antiseptic, compared to control
- Serious adverse events

Neonates:

- Adapted neonatal skin condition score (safety) (absolute score and grade)
- Temperature (change in absolute temperature and grade (hypothermia))
- Serious adverse events

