| 24 hours               | ✓                         | ✓        | ✓       |                                                                  |          |         | ✓                         | ✓        | ✓       |
| 28 hours               | ✓                         | ✓        | ✓       |                                                                  |          |         |                           |          |         |
| 32 hours               | ✓                         | ✓        | ✓       |                                                                  |          |         |                           |          |         |
| 48 hours               |                           |          |         |                                                                  |          |         | ✓                         | ✓        | ✓       |
| 72 hours               |                           |          |         |                                                                  |          |         | ✓                         | ✓        | ✓       |

\*Participants will be swabbed as per schedule or until delivery/birth (maternal strata) or discharge from the hospital (neonatal strata), whichever comes first.

#Newborns born to women from the maternal strata will be swabbed only once immediately after birth and will not receive any interventions.

Swabs will be vortexed in liquid transport medium, inoculated in serial dilutions on MacConkey and blood agar, and read after 24 hours incubation. Both total bacterial load (total CFU) and pathogen species will be recorded. Simultaneous inoculation onto extended spectrum beta-lactamase producing selective CHROMagar will be used to identify ESBL-E. Species identity will be confirmed by API.

Consent will be gained for use of samples in future microbiological analyses.

Swabs will be processed in the Malawi-Liverpool-Wellcome Trust microbiology laboratory, Blantyre. They will be securely couriered there from the trial site, using appropriate methods to control sample temperature. Two swabs will be taken and one disposed of after primary microbiological processing, and clones of bacteria will be kept in the Wellcome Trust research laboratory, Blantyre. The second

swab will be retained for up to 5 years to permit future microbiological analysis of the vaginal microbiota. Further details are outlined in the MOP.

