### **2.2. Secondary Outcome Measures**

#### **Maternal strata**

- Maternal toxicity – score and grade (tolerability and safety)
- Bacterial load in neonates exposed to maternal antiseptic, compared to control
- Serious adverse events

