#### Primary analysis

- The primary analysis population is intention-to-treat, including all randomised participants, regardless of treatment received.
- The outcome variable will be change in Total log10 CFU from baseline to assessment time point.
- The primary analysis will include all randomised participants with baseline and at least one post-baseline measure.
- The dependent variable will be total log CFU.
- The model will be a mixed effects model
- Fixed effects in the model will be:
  - Antiseptic (1% CHG, 2% CHG, OCT)
  - Frequency of application (once, multiple)
  - Time point of assessment: hour of swab (continuous; mfp will be used to assess linearity)
  - Baseline total CFU (continuous; mfp will be used to assess linearity)
- Individual will be fitted as a random effect to account for repeated measures within individuals. Goodness of fit of an unstructured covariance matrix will be assessed and used if it is clearly a better fit to the data than random intercepts only.
- Goodness of fit of an interaction between baseline total CFU and timepoint of assessment will be assessed and included in the model if clearly a better fit.
- Normally distributed errors will be fitted.
- The intercept (reference treatment category) will be once only 1% CHG as this is the lowest concentration of CHG, which is believed to be more readily available than OCT, and so would be the most straightforward to implement. The standard of care control will not be used as the reference as the sample size for this arm is lower than for the factorial arms and so power for comparisons is correspondingly lower.
- Comparison of effects between factorial arms will be assessed by testing whether the null hypothesis of no treatment effect can be rejected (equivalent to using the estimate and 95% confidence interval of the estimate of the difference to the intercept).
- Comparisons between other arms and between arms and the SOC arm may also be performed. There will be no formal correction for multiple testing but interpretation will take multiple testing into consideration.
- Model fitting will use restricted maximum likelihood (REML) and p-values are derived using the Kenward-Roger approximation.

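### SAP 4.7 sends newborns of enrolled mothers to a baseline-adjusted repeated-measures model with no standard-of-care level, but each has one swab occasion, no baseline and an outcome defined against control

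*Protocol*

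**What the plan says.** SAP 4.7 gives the whole analysis of this outcome in one sentence: "Analysis of bacterial load in neonates exposed to maternal antiseptic will be as per primary outcome analyses described above". No exception is attached.

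The analysis referred to is in SAP 4.6, under Primary analysis:

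- **Inclusion:** "The primary analysis will include all randomised participants with baseline and at least one post-baseline measure".
- **Outcome:** change in total log10 CFU "from baseline to assessment time point". A later bullet in the same list names total log CFU as the dependent variable.
- **Covariate:** baseline total CFU, as a continuous fixed effect.
- **Random effect:** "Individual will be fitted as a random effect to account for repeated measures within individuals".
- **Treatment terms:** three antiseptic preparations and two frequencies, with once-only 1% CHG as reference. Comparisons with SOC are optional.

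The footnote to Table 3 (Protocol 4.7.2) gives the sampling: "Newborns born to women from the maternal strata will be swabbed only once immediately after birth". Table 1 agrees, with a single post-delivery entry for the newborn's swabs.

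The outcome itself, in SAP 2.2 and Protocol 4.10.2.2, is "Bacterial load in neonates exposed to maternal antiseptic, compared to control". The protocol's Executive Summary words it differently: "Change in neonatal skin bacterial load in neonates exposed to maternal antiseptic, compared to control".

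**The concern.** A model built for serial swabs from one person has been assigned to people who have one swab occasion. The inclusion rule, the baseline covariate and the random effect all presuppose data that the schedule does not collect. The comparison that defines the outcome, against control, is also not among the model's listed terms.

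Protocol 4.7.2 says these swabs are there to estimate the effect of the maternal intervention in the newborn. The neonatal stratum excludes babies of enrolled mothers, so no other planned outcome measures bacterial load in the babies of treated mothers. If the text stands, the analyst must choose the model, covariate and contrasts later, in an open-label trial, when outcome data may already be available.

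**Working it through.** **1. Planned number.** SAP 1.1 and Protocol 4.5 give 7 arms of 21 mothers and one swabbed newborn per mother: 7 × 21 = 147. The Executive Summary total also reproduces: 3 × 147 = 441. The power figures in SAP 2.4 are for the randomised strata. None is given for this outcome, and they are not in question here.

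**2. Inclusion rule against schedule.** The rule needs at least one baseline and at least one post-baseline measure.

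| How the single newborn occasion is read | Baseline | Post-baseline | Newborns qualifying |
|---|---|---|---|
| As a post-birth measure | 0 | 1 | 0 of 147 |
| As the baseline | 1 | 0 | 0 of 147 |

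The neck and peri-rectal swabs do not form a pair over time. They are taken on the same occasion, and SAP 2.1 sums swab sites into one total.

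**3. Is a newborn baseline defined elsewhere?** SAP 3.1 takes baseline from screening or zero-hour records and has no rule for these newborns. No section nominates the mother's swab as a substitute.

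**4. Random effect.** With one record per newborn, the covariance matrix is V = (σ²_between + σ²_within) I. The likelihood depends only on the sum of the two variances, so they cannot be separated. On one simulated data set (n = 147, seven arms) the REML log-likelihood was:

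| Between / within variance | REML log-likelihood |
|---|---|
| 0 / 1 | −66.692 |
| 0.5 / 0.5 | −66.692 |
| 0.9 / 0.1 | −66.692 |

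**5. Contrast.** The outcome is defined against control. The model's antiseptic factor has three levels and its frequency factor two, none of them SOC. The 21 newborns of SOC mothers therefore have no stated place in the fixed effects.

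**6. What the data can support.** A cross-sectional regression on seven arms has 7 parameters and leaves 147 − 7 = 140 residual degrees of freedom. One linear maternal covariate leaves 139. Each antiseptic v SOC compares 2 × 21 = 42 newborns with 21; multiple v single compares 3 × 21 = 63 with 63. All of these are before any loss of swabs.

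**The case against.** The strongest reply is that a sensible analyst would adapt the model. The newborns are not themselves randomised; their mothers are, and the outcome is listed under the maternal stratum. On that view the mother's zero-hour swab is the baseline and the newborn swab is the later measure. SAP 4.6 also names total log CFU as the dependent variable, SAP 2.6 defines the summary as a difference in mean log CFU adjusted for baseline, and the first-measure and final-measure sensitivity analyses drop the random effect when there are no repeats.

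Part of this stands. A change score is not the only outcome the text supports, and the SAP recognises that single measures need no random effect. But no section makes the mother's swab the baseline, and those sensitivity analyses still model change from baseline. Elsewhere the SAP writes its exceptions out: SAP 4.8 names a substitute baseline for skin score, and SAP 4.11 names a different model for acquisition and loss of species. SAP 4.7 has no such exception.

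It is also fair that control comparisons are not absent from the plan. Protocol 4.10.4 mentions them, SAP 4.6 permits them, and its Bayesian section specifies posterior probabilities against SOC. The narrower point remains: the frequentist model assigned to this outcome lists no SOC level and leaves that comparison optional.

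A reader might also infer that the frequency contrast must be restricted to mothers still undelivered at the 4-hour application, because the single and multiple arms are treated alike until then. The documents do not support that. The primary population is intention-to-treat, SAP 2.6 expects that few women will labour for 32 hours, and no delivery times are given from which to size any dilution. Restricting the sample would change the question asked.

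**Conclusion.** The point holds as a specification error. On the literal rule, 0 of 147 newborns enter the assigned analysis, its random effect cannot be estimated, and the defining contrast with SOC is not a stated term. This rests on the wording of SAP 4.6 and 4.7 and the swab schedule, and on the planned one newborn per mother.

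A reader might infer that the outcome is lost or the trial's main results are affected. Neither follows. The swabs are collected regardless and can be analysed cross-sectionally; the outcome is secondary, in a pilot, with no power claim; and neither co-primary analysis depends on it. Nor does the Executive Summary's reference to change amount to a rival outcome, because both formal outcome lists name bacterial load. That difference is editorial. The text should be corrected before analysis, but the fault does not undermine the trial.

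**What to change.** Replace the cross-reference in SAP 4.7 with a model of its own:

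- **Outcome:** newborn total log10 CFU from the post-birth swabs, with no change score.
- **Model:** linear regression on the mother's randomised arm, by intention to treat, with SOC as a level and no random effect.
- **Covariate:** the mother's own zero-hour total log10 CFU, which is taken before any antiseptic is applied.
- **Contrasts:** each antiseptic v SOC as the planned comparison; multiple v single application estimated by intention to treat in all mothers.
- **Missing maternal baseline:** a stated rule for mothers without a usable zero-hour swab.

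As an editorial follow-on, align the Executive Summary wording with the outcome lists in Protocol 4.10.2.2 and SAP 2.2.

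The cost is SAP wording; no new data are needed. The drawback is the extra missing-data rule for a covariate whose precision gain is unknown: maternal vaginal and perineal load is a different measure from newborn neck and peri-rectal load, and the documents give no correlation between them.

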### **4.8. Secondary safety outcome analyses: skin score**

A summary table will be presented:

- Skin score at baseline: mean (SD) [N]
- Skin score at each assessment time point: mean (SD) [N]
- Change in total log10 CFU from baseline to each assessment time point: mean (SD) [N]

- Absolute skin score at baseline: n(%) 0, 1, 2...
- Absolute skin score at each assessment time point: n(%) 0, 1, 2...

#### **Skin score analysis**

- Analyses will be as per the primary outcome above, except baseline skin score will be used in place of baseline log CFU.
- Transformations may be performed if there is clear evidence of deviations from normally distributed errors in the safety outcome. If more than 70% of the safety endpoint are in one category, goodness of fit of alternative models (e.g. ordinal) will be considered

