### **All neonatal participants:**

Skin score: Skin will be assessed according to the skin score in Appendix I before each swab or antiseptic application at screening and once daily thereafter (at 24 and 48 hours) until discharge or 72 hours. For babies assigned to antiseptic application, skin score will also be assessed 30 minutes after antiseptic application.

Swab: Swabs (peri-rectal/rectal and cervical/neck) will be taken at baseline (0 hrs) and then at 24 hours, 48 hours, and 72 hours, or until discharge (whichever is sooner).

The timing of swabs will be recorded in a CRF. See MOP for further details on how to take swabs.

Final follow-up: On day 28 (+/- 7 days) after enrolment final follow up will occur either by phone call or hospital visit. If a hospital visit is chosen by the parents/carers, appropriate compensation will be provided for travel and time in line with local standard policies. Vital status will be ascertained, together with occurrence of serious adverse events (including clinically defined sepsis and any unscheduled visits to healthcare providers).

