### **Neonatal participants in multiple application arms:**

Temperature: Temperature will be measured before every antiseptic application and 15 minutes post application.

Antiseptic: The antiseptic will be applied to the whole body (except face) after each assessment and swabs: at baseline, and at 24 hours, 48 hours and 72 hours or discharge (more details [Section 4.6.2.3](#)).

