##### **Neonates:**

Safety will be assessed using a modified skin score which assesses the skin condition, and presence of erythema, dryness, and any other sign of skin damage (see [Appendix I](#))(46,47). This will be performed before each application of antiseptic and 30 minutes after application. The skin score will be considered as both an absolute value and graded. Skin score assessments will be performed once every day on all babies to provide unbiased comparisons across randomised groups.

Temperature will be monitored before and 15 minutes post every antiseptic application. For neonates in the once only and control arms temperature will be measured daily. Guidelines for repeating the temperature if it is out of range will be outlined in the clinical MOP.

Hypothermia will be graded as follows:

- Grade 1: 35.5 - 36.0C
- Grade 2: 35.4 - 35.0C
- Grade 3: 34.0 - 34.9C
- Grade 4:  $<34.0C$

Other adverse events will be monitored for daily and reported as described in [Section 5](#).

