### **4.9. Secondary safety outcome analyses: temperature**

Temperature analysis will be performed in the neonatal strata only.

A summary table will be presented for all babies randomised to treatment groups:

- Temperature at baseline: mean (SD) [N]
- Temperature pre-application at all time points: mean (SD) [N]
- Temperature at post-application at all time points: mean (SD) [N]

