#### **Temperature analysis**

- The analysis will include all babies randomised to treatment with at least one antiseptic application. Babies in the SOC group will be excluded from the analysis.
- The outcome variable will be:
  - Change in temperature from pre to post application.
- Fixed effects in the model will be:
  - Antiseptic (1% CHG, 2% CHG, OCT)
  - Frequency of application (once, multiple)
  - Day of trial (continuous; mfp will be used to assess linearity)
  - Temperature pre application (continuous; mfp will be used to assess linearity)
- Individual will be fitted as a random effect to account for repeated measures within individuals.
- Normally distributed errors will be fitted.
- Comparison of main effects within arms will be assessed using the estimate and 95% confidence interval of the comparison of differences between factors and in comparison, to SOC.
- The reference group will be 1% CHG once only as it is the most straightforward and conservative to implement. The SOC will not be used as the reference as the sample size for this arm is lower than for the factorial arms.

Additional analyses, as per the primary outcomes, may also be performed.

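### On its natural reading, SAP 4.8 leaves the neonatal 30-minute post-application skin score out of every comparison unless it reaches grade 3 or 4

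*Protocol*

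**What the plan says.** Protocol 4.7.3 (neonates) says of the skin score: "This will be performed before each application of antiseptic and 30 minutes after application". Protocol 4.7.1.2 limits the second score to treated babies: "For babies assigned to antiseptic application, skin score will also be assessed 30 minutes after antiseptic application". Standard-of-care (SOC) babies therefore have none. Protocol 4.7.3 gives the daily score a separate purpose: "Skin score assessments will be performed once every day on all babies to provide unbiased comparisons across randomised groups". In the multiple-application arms the antiseptic is applied "after each assessment and swabs: at baseline, and at 24 hours, 48 hours and 72 hours or discharge", so each daily score comes before that visit's application.

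The analysis is in SAP 4.8: "Analyses will be as per the primary outcome above, except baseline skin score will be used in place of baseline log CFU". The 4.8 summary table has rows for baseline and for each assessment time point. Its only change row is for log10 CFU, not for skin score. Elsewhere in the SAP, section 4.4 counts whether the post-application score was done, and section 4.10 counts skin scores of grade 3 or 4.

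Temperature is also measured before and after each application. For it, SAP 4.9 tabulates pre- and post-application values separately and takes as the model outcome "Change in temperature from pre to post application".

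**The concern.** The 30-minute score is the trial's direct measure of an acute skin reaction in neonates. SAP 4.8 gives it no table row of its own, no outcome and no model term, although the parallel safety measure in 4.9 has all three. Protocol 6.2.1 names safety concerns among the main reasons for the pilot, and the result is meant to help choose a regimen for a larger trial. If one antiseptic or concentration causes redness that has gone by the next morning, the planned model cannot show it.

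Milder scores are not trivial by the protocol's own standards. Protocol 4.5.1.2 treats a score of 2 in any domain as poor skin condition and excludes the baby at enrolment. Protocol 4.6.2.5 has the clinician consider interruption once a category exceeds 2.

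**Working it through.** The plan gives no figure for this point, so there is none to reproduce. The check has four steps.

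**1. Which scores does the 4.8 model use?** Four places bear on this:
- SAP 4.6, the model carried over, uses hour of swab as its time term.
- SAP 2.1 puts swabs before application.
- SAP 4.5 lists neonatal skin-score time points as days 0, 1, 2 and 3, with no 30-minute slot.
- Protocol 4.7.3 reserves the daily score for comparison across all groups.

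Together they point to daily pre-application scores only.

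**2. How many scores are then left out?** With 21 per arm, there are 3 × 21 = 63 single-application and 63 multiple-application neonates. Scheduled 30-minute scores are 63 × 1 + 63 × (number of applications in the multiple arms):
- last visit day 0: 63 + 63 = 126
- day 1: 63 + 126 = 189
- day 2: 63 + 189 = 252
- day 3: 63 + 252 = 315

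**3. Which applications have no later daily score?** In the multiple arms it is always the last one: 1 of 1, 1 of 2, 1 of 3 or 1 of 4 applications (100%, 50%, 33%, 25%) for a last visit on day 0, 1, 2 or 3. Single-arm babies have daily scores after their only application unless they leave before day 1.

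**4. What would pooling do?** Assume each application raises the 30-minute score by d, and that the rise has gone by the next daily score. With daily scores only, every contrast is 0. Now suppose the 30-minute scores were added to a random-intercept model with arm and linear time. All babies in an arm share one schedule, so the expected coefficients do not depend on the intraclass correlation (runs at 0, 0.3, 0.5 and 0.7 agree). The frequency coefficient is

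(difference in the share of 30-minute scores) × d − slope × (difference in mean assessment time).

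Full stay, time in days, 30 minutes = 0.5/24 = 0.0208:
- Single: times 0.0208, 1, 2, 3; mean 1.505; share 1/4; Sxy = −1.4844d; Sxx = 4.938.
- Multiple: times 1, 2, 3 and 0.0208, 1.0208, 2.0208, 3.0208; mean 1.726; share 4/7; Sxy = −0.8215d; Sxx = 7.394.
- SOC (21 babies): times 1, 2, 3; mean 2; share 0; Sxy = 0; Sxx = 2.
- Slope = 63 × (−1.4844 − 0.8215)d / [63 × (4.938 + 7.394) + 21 × 2] = −145.27d / 818.9 = −0.1774d.
- Multiple minus single = (0.5714 − 0.25)d + 0.1774d × (1.726 − 1.505) = 0.361d.
- SOC minus single = (0 − 0.25)d + 0.1774d × (2 − 1.505) = −0.162d.

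| Last visit | 30-minute share: SOC, single, multiple | Multiple − single | SOC − single |
|---|---|---|---|
| Day 1 | 0/1, 1/2, 2/3 | 0.288d | −0.150d |
| Day 2 | 0/2, 1/3, 3/5 | 0.332d | −0.176d |
| Day 3 | 0/3, 1/4, 4/7 | 0.361d | −0.162d |

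Without the SOC babies, multiple minus single is 0.288d, 0.334d and 0.363d. Antiseptic contrasts stay balanced, because antiseptic is crossed with frequency and each antiseptic has the same mix of schedules.

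**The case against.** The best defence is that the SAP follows the protocol. Protocol 4.10.2.2 defines the skin outcome as an absolute score and a grade, but the temperature outcome as a change, and Protocol 4.10.4 sets out a before-and-after model for temperature alone. The 30-minute check also serves bedside safety (Protocol 4.6.2.3), adverse events are monitored daily, and severe scores are counted in SAP 4.10. This stands to the extent that SAP 4.8 contradicts nothing and acute reactions do not go unwatched. It does not supply a comparison of milder acute reactions between regimens.

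A reader might infer that the plan pools 30-minute and daily scores, so that the frequency effect on skin is biased. The documents do not support that: the four places in step 1 of the working point to daily scores only. The 0.29d to 0.36d figures show what an unwary analyst would produce, not what the plan specifies.

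Two other parts of the SAP might seem to fill the gap. The 4.8 table's assessment time points could be stretched to include the 30-minute scores, but pre and post would still not be separated. The sensitivity analysis of time since last application (SAP 4.6) might be carried over, but 4.6 makes analyses beyond the primary optional, and it is not a pre-to-post comparison.

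It is also fair that the missing daily score after the last application comes from the visit schedule, not from SAP 4.8. That makes the 30-minute score the only scheduled score after that application.

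**Conclusion.** The point holds as a cheap improvement to a secondary safety analysis. As written, SAP 4.8 compares daily pre-application scores. The 126 to 315 scheduled 30-minute scores in 126 treated neonates inform no comparison below grade 3. What is lost is any milder reaction that settles before the next daily score, plus any milder reaction to the final application in the 63 multiple-arm neonates. A reaction that lasts to the next day is captured for every application except the last.

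A reader might go further and say that the skin analysis is biased or that the SAP departs from the protocol; neither is supported. The primary outcome is untouched.

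The counts assume every scheduled score is done. The size of any reaction, its duration and length of stay are not given in the documents, so the pooling figures are expressed in d and shown over a range of stays. The skin-score appendix is not in the text available, so how domain scores map to grades could not be checked.

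**What to change.** In SAP 4.8, for the neonatal stratum:

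1. Tabulate pre-application and 30-minute scores by day.
2. Among the six antiseptic arms, model the change from pre-application to 30 minutes as 4.9 does for temperature. Use the pre-application score as covariate, individual as a random effect, and no SOC comparison. Keep 4.8's existing ordinal alternative for when most scores fall in one category. Add application number: day 0 is the only day on which both frequencies have an application, so any build-up should be read from application number within the multiple arms, not from the frequency term.
3. State that the 30-minute scores do not enter the daily-score model that includes SOC. Pooling would distort the frequency and SOC contrasts.
4. Correct the change row in the 4.8 table from log10 CFU to skin score.

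The cost is a few lines of SAP text and one small extra model on scores already collected. The limitation is that the 30-minute score has no control group, so this analysis compares antiseptic regimens with each other only.
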